### Description of the intervention

Each RCT group consists of one or a combination of two/three of the following component as the intervention. The detail is shown in Table 1.

**Table 1 Tab1:** Summary of intervention in 3 groups

	Active referral group	Brief advice group	Control group
Active referral and referral card	✓		
Brief counselling with AWARD model	✓	✓	
Smoking harms and cessation leaflet	✓	✓	
General Advice and self-help booklet			✓

#### Active referral

Subjects will receive a referral card and be actively referred to one of the five major SC services in Hong Kong, including (1) Department of Health SC Services, (2) Tung Wah Group Hospital Integrated Center on SC, (3) Hospital Authority (HA) SC Clinics, (4) Pok Oi Hospital Chinese Medicine SC Services, and (5) University of Hong Kong Youth Quit-line. The details of each service are shown in Table 2. The well-trained SC ambassadors will explain the SC services to the subjects who will be asked to choose one of the SC services to be referred. Informed written consent and contact telephone number of the subjects will be obtained at the recruitment site, processed primarily in the university research office (including putting subjects’ information into computer), transferred to the collaborator - COSH (Hong Kong Council on Smoking and Health) and eventually destined at the selected service provider within 7 days. As proactive phone call service is not available in HA Clinics, subjects will be encouraged to make the appointment by themselves using a provided list of HA clinics contact addresses and telephone numbers. Research staff will monitor SC services use of the subjects and assist them to make or re-make the appointment if necessary in each follow-up (1-, 2-, 3- and 6- month).

**Table 2 Tab2:** Major smoking cessation services in Hong Kong

	Main services
Department of Health	Phone SC counselling managed by registered nurses.
Hospital Authority	SC clinics run by physicians and nurses.
	Free nicotine replacement therapy (NRT) and cessation drugs.
Tung Wah Group of Hospitals	SC clinics run by physician, nurses, and social worker.
	Free nicotine replacement therapy (NRT) and cessation drugs.
Pok Oi Hospital	SC clinics run by Chinese medical practitioners.
	Free acupuncture cessation therapy.
Youth Quit-line	Telephone counselling by well-trained youth smoking cessation counsellors.

#### Referral card

The pocket size referral card includes three major parts: (1) an introduction on each of the existing SC services; (2) practical information including the cessation hotline, address, operation hours of the SC clinics and address, and 3D barcodes of online SC services; and (3) highlights of information that may motivate smokers to use the service including assistance provided by experienced professional SC nurses or physicians; various cessation methods such as telephone counselling, face-to-face counselling, nicotine replacement therapy, cessation medication and acupuncture, which suit individual preference and are free of charge, convenient in access, and individual support if needed at follow-ups. The card is served as a reminder of information of SC services available.

#### AWARD model

Subjects will receive brief counseling using AWARD model that is an innovative, simple and effective model to guide the counselling [19]. It is more feasible than more lengthy or intensive counselling and can be delivered by lay or minimally trained person in community settings. AWARD model includes five components and can be delivered within a minute: (1) Ask about smoking history; (2) Warn about the high risk of smoking; (3) Advise to quit as soon as possible and comply with the decided quit date; (4) Refer smokers to smoking cessation services; and (5) Do it again.

#### Health warning and SC information leaflet

A 2-side colour printed A4 leaflet is designed to cover the most important messages to motivate participants to quit smoking. The content of the leaflet includes: (1) highlights of the absolute risk of death due to smoking; (2) the whole list of diseases caused by active and second-hand smoking; (3) ten horrible pictorial warnings of health consequences of smoking and secondhand smoke in one page to maximize the impacts; (4) benefits of smoking cessation and (5) simple messages to encourage participants to quit smoking and remind them to call the Department of Health SC [contact].

#### General advice and a self-help smoking cessation booklet

Participants will receive very brief, minimal and general smoking advice and a 12-page self-help smoking cessation booklet developed by the collaborator (COSH).

### Data collection

#### Baseline

Demographics including gender, age, marital status, number of children, type of residence, educational level, employment status and household income will be collected. Average number of cigarettes smoked per day, the age starting smoking and the usual time having the first cigarette smoked each day, attempts to quit or reduce, methods used in past quitting attempts, reasons of not currently using the SC services, readiness (decisional date to quit) and perceived importance, difficulties and confidence to quit smoking, and knowledge about smoking (e-cigarette and risk of smoking) will be collected using validated questions.

#### Follow-up

Follow-up telephone calls will be conducted at 1-, 2-, 3- and 6-months after the baseline to assess changes in smoking habits and progress of quitting especially the use of referred SC services. Subjects who reported not smoking in past 7 days at the 3- and 6-month follow-up will be furthered assessed by inviting their relatives/friends for verification (non-biochemical validation) and will be biochemically validated using the exhaled carbon monoxide and saliva cotinine tests.

### Outcome assessments

#### Primary outcome

The primary outcomes are self-reported 7-days PP quit rate at 3-month and 6-month follow-up. Subjects reporting not smoking in the past 7-days at 3-month and 6-month will be regarded as abstinence from smoking.

#### Secondary outcomes

Secondary outcomes at 3- and 6-month follow-up include:SC service use and indicators of use: calling a hotline, making an SC appointment, SC clinic attendance and counselling session attendance. Information of self-reported SC service use of active referral group will be verified with service providers’ records.Biochemical validated smoking abstinence: Smoking abstinence will be defined as exhaled carbon monoxide (CO) level <4 ppm and saliva cotinine level <10 ng/ml [25, 26].Smoking reduction: cigarette consumption reduced by at least 50 % compared with the baseline.

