### Sample-size calculation

The sample size calculation is based on the primary outcome of self-reported 7-day PP quit rate at the 3-month follow-up. Based on the previous similar studies conducted in the community in Hong Kong, the 3-month quit rate for the control group was approximately 10.0 % [19, 22, 23]. According to the RCT of active referral conducted by Borland et al. [10], the rate ratio of quit rate for the intervention and control group was 1.92 (intervention group: 12.3 %, control group: 6.9 %). Therefore, the effect size for the intervention in this study is set conservatively at 1.60. The quit rate for the intervention group (a combination of active referral and brief advice groups) versus the control group is 16.0 and 10.0 % respectively. To detect a significant difference of quit rate between intervention and control groups with a power of 80 and 5 % significance level, we will need 284 subjects per group. Assuming an intra-cluster correlation coefficient as 0.005 and retention rate of 70 % at the 3-month follow-up, the total sample size taking into account in the intra-cluster correlation within each recruitment session and attrition is 1291.

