### Data analysis

The main comparisons will be the self-reported 7 days PP quit rate among groups, which include: (1) Active referral plus brief advice vs. control: to test the bulk model of active referral with referral card plus brief counselling using AWARD model with smoking harms and cessation leaflet intervention effects; (2) Brief advice vs. control: to test brief counselling using AWARD model with smoking harms and cessation leaflet intervention effects; and (3) Active referral vs. brief advice: to test active referral with referral card intervention effects.

The intention-to-treat (ITT) principle will be used for outcome comparison between groups. Information missed at follow-up will be considered as non-quitters, non-reducers or do not use SC service if no records from the service providers are available for verification. Methods to handle missing cases (multiple imputations or complete case analysis) will depend on the proportion of actual percentages of the attrition rate. Baseline characteristics and outcome measures among groups at each endpoint will be compared using chi-square tests, Mann–Whitney tests and *t*-tests. Logistic regression will be used to predict quitting and models will be adjusted for baseline differences if necessary. Multi-level analysis method will be used to handle clustering effects.

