### Ethical approval and consent

This study has received ethical approval by the Institutional Review Board of the University of Hong Kong/ Hospital Authority Hong Kong West Cluster (IRB reference no.: UW15-332). The study poses minimal additional risk to study participants. Informed consent will be obtained from the participants for their participation in the study and agreement to allow us to transfer their contact information to their chosen SC service providers (for Group A only).

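### As written, service use is checked against provider records only in the active referral arm, and such records can override the missing-equals-non-user rule, so the between-arm comparison of this secondary outcome is not like for like

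*Protocol article*

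**What the plan says.** Three places in the protocol article bear on this.

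- **Secondary outcomes** lists, for 3 and 6 months, "SC service use and indicators of use: calling a hotline, making an SC appointment, SC clinic attendance and counselling session attendance". The next sentence fixes verification against provider records and names one arm: "Information of self-reported SC service use of active referral group will be verified".
- **Data analysis** applies intention to treat. Participants with missing follow-up are taken to "do not use SC service if no records from the service providers are available for verification". It adds: "Methods to handle missing cases (multiple imputations or complete case analysis) will depend on the proportion of actual percentages of the attrition rate". The section also says that outcome measures will be compared among groups.
- **Ethical approval and consent** describes consent that includes "agreement to allow us to transfer their contact information to their chosen SC service providers (for Group A only"). The label Group A is not explained in the text. It must mean the active referral group, since that is the only arm whose details go to a provider.

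No section provides for obtaining provider records in the brief advice or control arms.

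**The concern.** The missing-data rule depends on a data source that the text provides for in one arm. A participant in the active referral arm who used a service and was then lost can be recovered as a user from the provider's record. A similar participant in the brief advice or control arm has no such route under this rule. Among those who answer, self-report is checked in the active referral arm and taken at face value in the other two.

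Service use is the step through which active referral is meant to work. The Discussion says effectiveness will be judged not by abstinence alone but also by use of the referred service. The comparison most exposed is active referral against brief advice, which isolates the referral component. A difference there could come partly from how use was counted. Randomisation, blinded outcome assessors and multi-level modelling do not remove a difference in ascertainment between arms.

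**Working it through.** The protocol gives no expected rate, effect size or power for service use, so there is no figure of its own to reproduce. The check asks what the stated rules would show if true use were the same in every arm.

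**Inputs from the protocol**
- Retention: "retention rate of 70 % at the 3-month follow-up", so 30 % missing.
- 1291 participants in three arms: 1291/3 ≈ 430 per arm.
- 66 sessions: 1291/66 = 19.56 per session. With the intra-cluster correlation of 0.005, the design effect is 1 + 18.56 × 0.005 = 1.093, and the effective size is 430/1.093 ≈ 393 per arm. That correlation was set for the quit outcome; using it here is an assumption.
- Service use among Hong Kong smokers in 2015: 5.0 % (Background).

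**Assumptions**
- True use u = 5 %, 10 % or 20 %, equal in all arms and equal in lost and retained participants.
- Equal retention in all arms.
- A fraction f = 0, 3 % or 5 % of true non-users report use.
- Records, where sought, capture every lost user and expose every false report.

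**Observed use**
- Other arms: 0.70 × [u + (1 − u)f].
- Active referral, lost users recovered and unconfirmed reports recoded: 0.70u + 0.30u = u.
- Active referral, recovery only: 0.70 × [u + (1 − u)f] + 0.30u.

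| u | f | Other arms | Active, both | Ratio, both | Ratio, recovery only |
|---|---|---|---|---|---|
| 5 % | 0 | 3.5 % | 5.0 % | 1.43 | 1.43 |
| 5 % | 3 % | 5.5 % | 5.0 % | 0.91 | 1.27 |
| 5 % | 5 % | 6.8 % | 5.0 % | 0.73 | 1.22 |
| 10 % | 0 | 7.0 % | 10.0 % | 1.43 | 1.43 |
| 10 % | 3 % | 8.9 % | 10.0 % | 1.12 | 1.34 |
| 10 % | 5 % | 10.2 % | 10.0 % | 0.99 | 1.30 |
| 20 % | 0 | 14.0 % | 20.0 % | 1.43 | 1.43 |
| 20 % | 3 % | 15.7 % | 20.0 % | 1.28 | 1.38 |
| 20 % | 5 % | 16.8 % | 20.0 % | 1.19 | 1.36 |

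With f = 0 the ratio is 1/0.70 = 1.43 whatever u is. It would be 1/0.80 = 1.25 at 80 % retention and 1/0.90 = 1.11 at 90 %. Recoding without any recovery (active arm 0.70u) gives 0.51 to 0.89 for f of 3 to 5 %.

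**False-positive rate at f = 0, full capture.** With observed proportions a (active) and b (other), SE = √{[a(1 − a) + b(1 − b)]/393}, z = (a − b)/SE, and the two-sided rejection probability is 1 − Φ(1.96 − z) + Φ(−1.96 − z).
- u = 5 %: SE 0.0144, z = 0.015/0.0144 = 1.04, rate 18 %.
- u = 10 %: SE 0.0199, z = 0.030/0.0199 = 1.51, rate 33 %.
- u = 20 %: SE 0.0267, z = 0.060/0.0267 = 2.25, rate 61 %.

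If records capture only half of the lost users, active use is 0.85u, the ratio is 0.85/0.70 = 1.21, and the same formula gives about 8 %, 12 % and 21 %. At u = 10 % and f = 5 % with recoding, the two effects nearly cancel and the rate is about 5 %.

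**One rule for all arms.** Every arm then shows 0.70 × [u + (1 − u)f], and the ratio is 1.00 for every u and f.

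**The case against.** A reader might infer something stronger: that a lost service user outside the active referral arm is always counted as a non-user, that over-reporting is corrected in one arm only, and that the result is a known inflation of about 43 % in favour of active referral. The documents do not support that, for five reasons.

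- That records are confined to one arm is an inference from the verification sentence naming one group. Nothing expressly rules out records elsewhere, and the missing-data rule itself carries no arm restriction. The consent clause concerns passing contact details to a provider so that the referral can happen, not retrieving usage records, so it is only indirect support.
- The text says self-report will be verified. It does not say that a contradicted report is recoded; verification might be reported only as agreement.
- The sentence on multiple imputation or complete case analysis leaves another route open. A complete case analysis would involve no recovery. The sentence does not say whether it covers service use.
- Calls are also planned at 1 and 2 months (Follow-up). A user lost by month 3 may already have reported use, and the text does not say how such reports count.
- The ratio of 1.43 is the extreme case: full capture and no over-reporting.

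All of this stands, and it limits how firmly direction and size can be stated. It does not remove the point. The article is condensed, but on this matter it is not silent: it states an arm-specific check and a missing-data rule that can draw on it. Nor does possible cancellation of two opposite errors make the comparison valid.

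**Conclusion.** The point holds in this limited form. Followed as written, the text ascertains service use differently by arm, and the between-arm comparison is not like for like. The sign of the net bias is not determined. The range of about 0.73 to 1.43 for a true ratio of 1.00 rests on assumed use, assumed over-reporting, equal 70 % retention and full record capture. The false-positive rates of 18 %, 33 % and 61 % belong to the upper end of that range and should not be quoted as the expected effect; at the one rate of use the protocol gives, 5.0 %, the figure is 18 %. Service use is a secondary outcome. The self-reported quit rate, on which the main comparisons rest, is not affected. The change should be made, but it does not threaten the trial's main result.

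**What to change.** In Secondary outcomes and Data analysis, define the between-arm service-use outcome on self-report in all three arms, with one stated missing-data rule and neither recovery nor recoding from provider records. Report provider-verified use, and its agreement with self-report, descriptively within the active referral arm.

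This changes wording only and needs no new data. The price is that the between-arm figure stays unverified. A common rule also does not protect against retention or over-reporting that truly differs by arm, so retention should be shown by arm beside the result. Seeking consent for provider records in all three arms would also restore comparability and would verify the comparison, but it needs new consent wording and additional data collection.

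### Validated abstinence requires low cotinine with no provision for NRT users, which probably biases this secondary outcome against active referral

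*Protocol article*

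**What the plan says.** Secondary outcomes fixes validated abstinence as "exhaled carbon monoxide (CO) level <4 ppm and saliva cotinine level <10 ng/ml". Follow-up sets out who is tested: participants reporting 7-day abstinence at 3 and 6 months "will be biochemically validated using the exhaled carbon monoxide and saliva cotinine tests", and relatives or friends are also asked to confirm. Neither section says how a participant using NRT or another nicotine product is to be classified, and nothing elsewhere in the article does.

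Table 1 gives active referral and the referral card to the active referral arm only. For that arm, Active referral states: "Subjects will receive a referral card and be actively referred to one of the five major SC services in Hong Kong". For two of the five services, Hospital Authority and Tung Wah, Table 2 lists "Free nicotine replacement therapy (NRT) and cessation drugs". The Referral card section says the card describes "various cessation methods such as telephone counselling, face-to-face counselling, nicotine replacement therapy, cessation medication and acupuncture". Service use in this arm is supported up to and including the test times: "Research staff will monitor SC services use of the subjects and assist them to make or re-make the appointment if necessary in each follow-up", that is, at 1, 2, 3 and 6 months.

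The brief advice arm is not cut off from services. The AWARD model, given in both intervention arms, includes the step "Refer smokers to smoking cessation services", and the leaflet points to the Department of Health line. Control participants receive very brief general advice and a booklet.

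**The concern.** Cotinine is a breakdown product of nicotine and does not show whether the nicotine came from tobacco or from NRT. This is general pharmacology and is not stated in the article. Because both tests must be passed, someone who has stopped smoking, reports it truthfully and has a low CO reading can still fail on cotinine because of NRT, and is then counted as not abstinent.

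NRT is among the treatments to which active referral can lead, so the error need not fall equally on the arms. The primary outcome is self-reported and only the outcome assessors are blinded, so the validated outcome is where a reader will look for confirmation. If true quitters are removed more often from the active referral arm, a real effect could look unconfirmed, or truthful participants could look like misreporters.

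**Working it through.** **Text check.** The definition is complete as printed: two tests, two cut-offs, joined by a requirement to meet both. Applied literally, it classes a true quitter with NRT-derived cotinine of 10 ng/ml or more as not abstinent. The route to free NRT by active referral exists in one arm only (Table 1 with Table 2).

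**Illustration of size.** The article gives no expected validated rate and no figure for NRT use among quitters, so there is no figure of its own to reproduce.

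Inputs:
- Abstinence rates of 16% and 10%, from Sample-size calculation. There they are self-reported rates for the two intervention arms combined and for control. Here they stand in for true abstinence in the active referral and control arms.
- f_A and f_C, the shares of true quitters in the active referral and control arms who fail cotinine because of NRT at the test. These are assumed.

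Formulas:
- Observed validated rate = true rate × (1 − f)
- Observed rate ratio = 1.60 × (1 − f_A) / (1 − f_C)

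| f_A | f_C | Active referral | Control | Rate ratio |
|---|---|---|---|---|
| 0% | 0% | 16.0% | 10.0% | 1.60 |
| 5% | 5% | 0.16 × 0.95 = 15.2% | 0.10 × 0.95 = 9.5% | 1.60 |
| 10% | 5% | 0.16 × 0.90 = 14.4% | 9.5% | 1.52 |
| 20% | 5% | 0.16 × 0.80 = 12.8% | 9.5% | 1.35 |

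The second formula shows that only the difference between arms biases the ratio. Equal shares leave it at 1.60, although the risk difference shrinks slightly (15.2 − 9.5 = 5.7 points instead of 6.0). The ratio is pulled towards 1 whenever f_A exceeds f_C and would move the other way if f_C were larger. The same factor, with the brief advice share in place of f_C, applies to active referral versus brief advice.

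The illustration leaves out refusal of testing and smokers who pass both tests.

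**The case against.** **The article may have been condensed.** The full protocol and analysis plan are not shown, and a sub-rule for NRT users might be there. The cut-offs also rest on two cited sources that cannot be consulted here. This does not remove the point. The definition is printed in full with numerical thresholds, and as printed it misclassifies these participants. If a sub-rule exists elsewhere, it belongs in this definition.

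**The effect may be small.** This stands, and it limits the claim. Three of the five services list no NRT. Hospital Authority referrals must book for themselves, so only one NRT-giving service is reached by a full active referral. Participants choose the service. To be misclassified, a quitter must have attended, received NRT, stopped smoking and still be using it when tested at 3 or 6 months. No passage supports a particular share.

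**Stronger readings are not supported.** A reader might infer that misclassified quitters fall mainly in the active referral arm. That is an inference from the design: NRT use in the other arms is unknown, and the brief advice arm also has a referral step. A reader might also convert the illustration into lost power. The protocol makes no power claim for validated abstinence, and the planning rates are self-reported and for the combined intervention arms. Nor is this the only verification, since relatives or friends are also asked, although it is the only biochemical one.

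**The present rule is conservative and a CO-only rule is lenient.** This also stands. In the likely direction, the current rule can hide an effect of active referral but does not create one. A CO-only route for declared users is opened by self-report and would probably be used more in the active referral arm. That calls for showing the definitions side by side. It is not a reason to keep the current rule alone.

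**Conclusion.** The point holds for the secondary outcome of validated abstinence. The stated rule classes true quitters still using NRT at the 3- or 6-month test as not abstinent, and the design makes this probably more frequent in the active referral arm. The likely bias is against active referral. Self-reported 7-day abstinence, the sample size and the main comparisons do not depend on cotinine and are unaffected.

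The direction rests on two assumptions: that NRT use at the test can push cotinine to the cut-off or above, and that such use is more common among active referral quitters. The size is not known. The illustrative rate ratios run from 1.60 with equal use, through 1.52, to 1.35 at 20% versus 5%. They show sensitivity to the assumption and are not an estimate for this trial. The change is worth making because it is cheap and this is the biochemical check on a self-reported primary outcome.

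**What to change.** 1. At each validation (3 and 6 months), ask participants in all three arms whether they used NRT or any other non-smoked nicotine in the past 7 days.
2. Define validated abstinence as CO <4 ppm alone for declared users, and as CO <4 ppm with saliva cotinine <10 ng/ml for everyone else.
3. Report beside it, for every arm, the results under the current both-tests rule and under CO <4 ppm alone for all participants.

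The cost is one question and a few lines in the outcome definition. Both tests are already planned, so the two comparison analyses need no new measurements.

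The downside is that CO alone is a less sensitive check, triggered by an unverified answer and likely to be applied more often in the active referral arm. It could therefore favour that arm. CO alone for everyone applies one test to all arms, and the both-tests rule keeps the conservative result. If the conclusions differ across the three, the report should say so.
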